#### Table 9. Operational Definitions of Covariates

| **Characteristic** | **Details** | **Type of variable** | **Assessment window** | **Care Settings¹** | **Code Type^2^** | **Diagnosis Position^3^** | **Applied to study populations:** | **Measurement characteristics/validation** | **Source for algorithm** |
| --- | --- | --- | --- | --- | --- | --- | --- | --- | --- |
| Age | (cohort entry year - year of birth) | Continuous | [0,0] | n/a | n/a | n/a | Exposure, comparator 1, comparator 2 | n/a | n/a |
| Sex | Male, Female | Categorical | [0, 0] | n/a | n/a | n/a | Exposure, comparator 1, comparator 2 | n/a | n/a |
| 2^nd^ vs 3^rd^ line therapy | If Drug A/B initiator and prior exposure to Drug C 🡪 3^rd^ line, otherwise 2^nd^ line  If Drug C initiator 🡪 2^nd^ line  If Drug D initiator 🡪 3^rd^ line | Binary | [-∞, 0] | *n/a* | *n/a* | *n/a* | Exposure, comparator 1, comparator 2 | No validation study | n/a |
| To be added |  |  |  |  |  |  |  |  |  |

^1^ IP = inpatient, OP = outpatient, ED = emergency department, OT = other, n/a = not applicable

^2^ See appendix for listing of clinical codes for each study parameter

^3^ Specify whether a diagnosis code is required to be in the primary position (main reason for encounter)

- 1. Data analysis

#### 7.5.1 Context and rationale for analysis plan

We conduct propensity score matched analysis with Cox proportional hazards models for time-to-event outcomes (mortality, progression free survival, toxic adverse effects). Patients with missing age/sex are excluded. Missing values on health-related quality of life at baseline will be imputed using multiple imputation.

The models for analysing health related quality of life and resource use are to be discussed and developed in a later version of this protocol.

#### Table 10. Primary, secondary, and subgroup analysis specification

1. **Primary analysis**

| **Hypothesis:** | Exposure to Drug A/B increases risk of death relative to SoC comparators with the lower bound of the 95% confidence interval for the hazard ratio above 1.0. |
| --- | --- |
| **Exposure contrast:** | Exposure, comparator 1 (concurrent) |
| **Outcome:** | Death |
| **Analytic software:** | SAS 9.4: PHREG, PROC LOGISTIC, Pharmacoepi Toolbox nearest neighbor matching macro (http://www.drugepi.org/dope-downloads/) |
| **Model(s):**  ***(provide details or code)*** | *Outcome model:* Cox proportional hazards  followuptime*status(0) = exposure  *Propensity score model*: logistic regression  Exposure = Risk factors to be determined |
| **Confounding adjustment method** | ***Name method and provide relevant details, e.g. bivariate, multivariable, propensity score matching (specify matching algorithm ratio and caliper), propensity score weighting (specify weight formula, trimming, truncation), propensity score stratification (specify strata definition), other.*** |
|  | We will use logistic regression to estimate a propensity score using covariates that will be determined and recorded in an updated protocol before conducting inferential analysis. We will use this propensity score to nearest-neighbor match with a caliper of 0.2 standard deviations on the logit scale of the propensity score using the nearest neighbor algorithm from the Pharmacoepi Toolbox. |
| **Missing data methods** | ***Name method and provide relevant details, e.g. missing indicators, complete case, last value carried forward, multiple imputation (specify model/variables), other.*** |
|  | Patients with missing or unknown sex will be excluded. Multiple imputation will be used to impute missing data on health related quality of life at baseline. We assume that if no relevant claims diagnoses/procedures are present in the registry data, that the patient does not have the condition/procedure. |
| **Subgroup Analyses** | ***List all subgroups*** |
|  | 1. 2^nd^ vs 3^rd^ line of therapy |

1. **Secondary Analysis 1**

| **Hypothesis:** | Exposure to Drug A/B increases risk of progression free survival relative to SoC comparators with the lower bound of the 95% confidence interval for the hazard ratio above 1.0. |
| --- | --- |
| **Exposure contrast:** | Exposure, comparator 1 (concurrent) |
| **Outcome:** | Progression free survival |
| **Analytic software:** | SAS 9.4: PHREG, PROC LOGISTIC, Pharmacoepi Toolbox nearest neighbor matching macro (http://www.drugepi.org/dope-downloads/) |
| **Model(s):**  ***(provide details or code)*** | *Outcome model:* Cox proportional hazards  followuptime*status(0) = exposure  *Propensity score model*: logistic regression  Exposure = Risk factors to be determined |
| **Confounding adjustment method** | ***Name method and provide relevant details, e.g. bivariate, multivariable, propensity score matching (specify matching algorithm ratio and caliper), propensity score weighting (specify weight formula, trimming, truncation), propensity score stratification (specify strata definition), other.*** |
|  | We will use logistic regression to estimate a propensity score using covariates that will be determined and recorded in an updated protocol before conducting inferential analysis. We will use this propensity score to nearest-neighbor match with a caliper of 0.2 standard deviations on the logit scale of the propensity score using the nearest neighbor algorithm from the Pharmacoepi Toolbox. |
| **Missing data methods** | ***Name method and provide relevant details, e.g. missing indicators, complete case, last value carried forward, multiple imputation (specify model/variables), other.*** |
|  | Patients with missing or unknown sex will be excluded. Multiple imputation will be used to impute missing data on health related quality of life at baseline. We assume that if no relevant claims diagnoses/procedures are present in the registry data, that the patient does not have the condition/procedure. |
| **Subgroup Analyses** | ***List all subgroups*** |
|  | 1. 2^nd^ vs 3^rd^ line of therapy |

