#### Table 2 Primary and secondary objectives and research questions

1. **Primary objective and research question**

| **Objective:** | To compare overall survival (OS) in patients > 18 years with metastatic [organ]carcinoma with a biomarker Y+ mutation who have shown progression after first line treatment and have indicated informed consent for longitudinal observational data collection as part of the XYZ Registry and are treated with a combination of Drug A and Drug B compared to controls who are treated with standard care for a period of a maximum of 2 years (or 4 years). Comparator patients will be included retrospectively as well prospectively. |
| --- | --- |
| **Hypothesis:** | Overall survival will be improved with Drug A and Drug B compared to standard of care. |
| **Population *(mention key inclusion-exclusion criteria):*** | Patients with biomarker Y+ positive metastatic [organ] cancer who progressed after at least of one line of treatment |
| **Exposure:** | Initiation of Drug A in combination with Drug B |
| **Comparator:** | Standard of care. In [anonymous country], SoC second line therapy is Drug C or in third line the SoC is Drug D. There will be 2 comparator arms. One will be initiation of Drug C or Drug D using concurrent years of data with the exposure arm. The other comparator group will be initiatiors of Drug C or Drug D using historical controls from years of data prior to availability of Drug A/B. |
| **Outcome:** | Overall Survival (OS) |
| **Time *(when follow up begins and ends):*** | Follow up from day after initiation of therapy until the first of outcome, discontinuation, add/switch therapy, disenrollment, end of study period, nursing home admission, death, progression of therapy, others to be discussed. |
| **Setting:** | Outpatient care |
| **Main measure of effect:** | Hazard Ratio (to be discussed). |

1. **Secondary objective 1 and research question**

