#### 7.4.4 Context and rationale for covariates (confounding variables and effect modifiers, e.g. risk factors, comorbidities, comedications)

We will adjust for major confounders such as age and sex. In the primary analysis, we will balance the Drug A/B exposed group (2^nd^ or 3^rd^ line) and Drug C (2^nd^ line) or D (3^rd^ line) SoC comparator group on prior exposure to Drug C, which will be an indicator of line of therapy. Patients who initiate Drug A/B and have prior exposure to Drug C are assumed to be 3rd line therapy. Those without prior exposure to Drug C are assumed to be on 2^nd^ line therapy. SoC initiators of Drug C (2nd line) will not have prior exposure because of the washout imposed to define new initiation and will be considered on 2^nd^ line therapy, in accordance with guidelines for use. SoC initiators of Drug D will be considered on 3rd line therapy regardless of whether they had prior exposure to Drug C (2^nd^ line therapy). Other covariates are to be determined after additional discussion.

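### One propensity score over the pooled Drug C or Drug D arm does not secure balance within line of therapy, so the planned 2nd- and 3rd-line hazard ratios can differ spuriously

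*Protocol*

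**What the plan says.** Protocol Table 2 describes a standard of care that depends on line: "SoC second line therapy is Drug C or in third line the SoC is Drug D". Section 7.4.1 says the same. Table 2 nevertheless defines a single concurrent comparator arm: "One will be initiation of Drug C or Drug D using concurrent years of data with the exposure arm".

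Table 10 contrasts A/B with that whole arm in the primary analysis. It estimates one logistic propensity score, "using covariates that will be determined and recorded in an updated protocol before conducting inferential analysis", and matches on the score alone: "We will use this propensity score to nearest-neighbor match with a caliper of 0.2 standard deviations on the logit scale of the propensity score". The outcome model is "followuptime*status(0) = exposure", with no line term, line stratum or line interaction. The only subgroup entry is "1. 2^nd^ vs 3^rd^ line of therapy". The first secondary analysis (progression-free survival) repeats the whole specification.

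Line is not ignored. Section 7.4.4 says that "we will balance the Drug A/B exposed group (2^nd^ or 3^rd^ line) and Drug C (2^nd^ line) or D (3^rd^ line) SoC comparator group" using prior Drug C as the marker of line, and Table 9 lists line as a binary covariate.

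**The concern.** The line-specific HRs are the estimates that set A/B against the treatment it would replace in each line. The matching rule does nothing to keep a 2nd-line A/B patient with Drug C or a 3rd-line A/B patient with Drug D. Line is at most one term in a common score.

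Choosing A/B over C and choosing A/B over D are different decisions, so the same patient characteristic may push towards A/B in one line and away from it in the other. A score with main effects only averages the two tendencies. It can balance a covariate over the whole matched set and leave it unbalanced in opposite directions within each line. The line subgroups would then suggest that the effect depends on line when it does not. Section 5 says that the results may influence coverage and reimbursement, where such a difference could mislead.

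**Working it through.** **1. The plan's own figure, for scale.** Section 7.9 gives about 5,000 exposed patients, 35% deaths at one year, 1:1 matching and more than 80% power for HR 0.90. Two-sided alpha of 0.05 is assumed from the 95% interval. Schoenfeld: power = Φ(|ln HR|·√d / 2 − 1.96). With d = 10,000 × 0.35 = 3,500, power = Φ(0.1054 × 59.16 / 2 − 1.96) = Φ(1.157) = 87.6%. The claim reproduces, for the pooled contrast only. The protocol gives no line split. A line with 30%, 50% or 70% of the patients would have 1,050, 1,750 or 2,450 events and 40.0%, 59.6% or 74.1% power for the same HR.

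**2. Does balancing line keep pairs within line?** Simulated 1:1 nearest-neighbour matching, caliper 0.2 SD of the logit, 5,000 A/B and 10,000 pooled C or D patients, line in the score with other covariates (comparator size, line shares and covariate shifts assumed). Share of 2nd-line A/B patients paired with a Drug D patient, by 3rd-line share in A/B versus standard of care:

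| 50/50 | 50/40 | 50/30 | 30/50 | 50/20 | 30/70 |
|---|---|---|---|---|---|
| 50% | 42% | 27% | 20% | 12% | 5% |

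With only age, sex and line in the score, the share was 51% at 50/50, 24% at 50/40, 4% at 50/30 and about 0% at 30/70. In every run the overall line mix agreed to within 0.5 points. Balance on line is therefore not pairing within line.

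**3. Do crossing pairs bias the HRs?** Four sets of simulations with no drug effect, 40% of patients in 3rd line and a covariate for poor performance status. In set A: 10,000 patients, about 35-40% on A/B, score on age, sex, performance status and line, one-year follow-up, hazard multiplied by exp(0.5) for 3rd line and exp(0.7) for poor performance status, 40 cohorts per scenario. Sets B to D chose their remaining settings independently (B: 30 cohorts, Monte Carlo SE about 0.01; C: 60 cohorts). Selection is the log-odds of A/B for poor performance status, against C / against D.

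| Set | Selection | Score | Pairs crossing | HR 2nd | HR 3rd | HR overall |
|---|---|---|---|---|---|---|
| A | equal | main effects | 36% | near 1.00 | near 1.00 | near 1.00 |
| B | equal | main effects | 48% | 1.00 | 1.01 | – |
| A | −0.7 / +0.3 | main effects | 14% | 0.97 | 1.06 | 1.02 |
| B | −0.7 / +0.3 | main effects | 33% | 0.93 | 1.08 | 1.01 |
| C | −0.7 / +0.3 | main effects | – | 0.94 | 1.10 | 1.02 |
| D | −0.7 / +0.3 | main effects | – | 0.94 | 1.08 | 1.00 |
| B | −0.7 / 0 | main effects | 42% | 0.96 | 1.05 | – |
| C | −0.7 / −0.4 | main effects | – | 0.98 | 1.03 | 1.01 |
| B | −0.3 / −0.7 | main effects | – | 1.03 | 0.98 | – |
| C | −0.7 / +0.3 | with line interaction | 39% | 1.01 | 1.00 | 1.00 |
| A | −0.7 / +0.3 | within line | 0% | 1.00 | 1.00 | 1.00 |
| B | −0.7 / +0.3 | within line | 0% | 0.99 | 0.99 | – |

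The bias does not follow the crossing share: 48% crossing gave none, 14% gave some, and an interaction term removed it with 39% of pairs still crossing. It follows the missing interaction. Under −0.7 / +0.3 with main effects only, the spurious ratio of 3rd-line to 2nd-line HR runs from 1.06 / 0.97 = 1.09 to 1.10 / 0.94 = 1.17.

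**4. Is line one variable in the protocol?** Section 7.4.4 balances on prior Drug C, but it and Table 9 count every Drug D initiator as 3rd line, and Table 3 does not require prior C for them. A Drug D patient without prior C therefore has the same prior-C value as a 2nd-line A/B patient. With 50/50 line shares and prior C in the score, if 10% of Drug D initiators lack prior C, the 3rd-line share after matching is 50% in A/B and 54% in standard of care. At 40% it is 47% and 62%.

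**The case against.** The strongest reply has four parts.

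- **One pooled objective.** Table 2 states one objective, one hypothesis and one effect measure. Its two comparator arms are concurrent and historical, not C and D. A reader might infer two separate line-specific questions; the text does not pose them. This stands: the line-specific contrasts enter only as a subgroup.
- **Line balance is planned.** A reader might infer that the pooled HR is confounded by line. The documents do not support that: with the Table 9 line variable in the score, the overall line mix balanced in every run.
- **Crossing pairs are harmless in themselves.** Propensity matching balances groups rather than making pairs alike, and the Cox model in Table 10 is unpaired. Step 3 confirms this, so the finding cannot rest on broken pairs.
- **The score is still open.** Table 10 leaves the covariates to a later update, so a main-effects score is an assumption, and interactions or re-matching within subgroups could still be added. This also stands. However, the single score, score-only matching, exposure-only model and line subgroup are written as decided, and adding further main effects would not secure balance within line.

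The simulated size also rests on invented inputs. Performance status, the 40% share in 3rd line and the selection strengths are not in the protocol. With milder selection in the same direction (−0.7 / −0.4), HRs of 0.98 and 1.03 are small against a single-study standard error of about 0.05.

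**Conclusion.** The point holds as a limited one. The matching rule in Table 10 does not secure covariate balance within line, and line is the only planned subgroup. If selection into A/B differs by line and the score lacks line interactions, the line-specific HRs can move apart under no effect: about 0.93 to 0.97 in 2nd line and 1.06 to 1.10 in 3rd line with opposed selection, smaller with milder differences, and little or none when selection is similar. These sizes illustrate a mechanism on assumed inputs and do not predict the study's bias. For scale, the study is powered for HR 0.90.

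The primary pooled HR is barely touched by this mechanism (1.00 to 1.02). That presumes line is coded consistently, which section 7.4.4 and Table 9 do not yet ensure. This is a worthwhile and cheap improvement to the line-specific estimates, not a demonstrated error in the primary analysis.

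**What to change.** First reconcile section 7.4.4, Table 9 and Table 3, so that prior Drug C and line of therapy are either one variable or two with stated roles. Matching within line on an inconsistent definition would build the inconsistency in.

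Then, in Table 10, for both the primary and the first secondary analysis:

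- estimate the propensity score separately in 2nd-line and 3rd-line patients, or include line interactions and match exactly on line;
- match A/B only to the same-line comparator, with the same caliper;
- stratify the primary Cox model by line;
- use the same matched sets for the line subgroups, and report covariate balance within each line.

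This takes about one sentence and one extra call of the matching macro, and Table 10 already announces a protocol update before inferential analysis. The downside is fewer pairs: under 1% lost in some simulations, and (3,843 − 3,740) / 3,843 = 2.7% in set A. Applied to the plan's own figures, 3,500 × 3,740 / 3,843 = 3,406 events, and power for HR 0.90 falls from 87.6% to Φ(0.1054 × 58.36 / 2 − 1.96) = 86.7%, still above the stated 80%.

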#### Table 11. Sensitivity analyses – rationale, strengths and limitations

|  | **What is being varied? How?** | **Why?  (What do you expect to learn?)** | **Strengths of the sensitivity analysis compared to the primary** | **Limitations of the sensitivity analysis compared to the primary** |
| --- | --- | --- | --- | --- |
| Sensitivity Analysis 1 | To be discussed | To be discussed | To be discussed | To be discussed |

- 1. Data sources

#### 7.6.1 Context and rationale for data sources

**Reason for selection:** We are using the XYZ Data Registry in [anonymous country] because this data was specifically collected to address the research objectives of this protocol.

**Strengths of data source(s):** This data will include longitudinal electronic health records, insurance claims, death records, and patient reported outcomes for a national registry of patients with metastatic [organ] carcinoma.

**Limitations of data source(s):** Free-text notes are available but require further NLP processing to extract some relevant characteristics. Missing data methods will be necessary to deal with laboratory results, some of which have a high proportion of missingness.

**Data source provenance/curation:** The registry has detailed documentation about the data sources, linkage, provenance, quality assurance, and financing (www.redactedlink.com).

#### Table 12. Metadata about data sources and software

|  | **Data 1** | **Data 2** |
| --- | --- | --- |
| **Data Source(s):** | XYZ Data Registry (concurrent/prospective) | XYZ Data Registry (historical) |
| **Study Period:** | Jan 1, 2021- Dec 31, 2022 | Jan 1, 2019- Dec 31, 2020 |
| **Eligible Cohort Entry Period:** | Jan 1, 2021- Dec 31, 2022 | Jan 1, 2019- Dec 31, 2020 |
| **Data Version (or date of last update):** | V2.0 – V5.0 | V1.0 |
| **Data sampling/extraction criteria:** | All patients > 18 years with metastatic [organ] carcinoma with a biomarker Y+ mutation who have shown progression after first line treatment and are treated with a combination of Drug A/B or with standard care | All patients > 18 years with metastatic [organ] carcinoma with a biomarker Y+ mutation who have shown progression after first line treatment and are treated with standard care |
| **Type(s) of data:** | Patient registry data including linked electronic health records, insurance claims, death, and patient reported outcomes | Patient registry data including linked electronic health records, insurance claims, death, and patient reported outcomes |
| **Data linkage:** | Linked based on universal patient identifier in [anonymous country] | Linked based on universal patient identifier in [anonymous country] |
| **Conversion to CDM*:** | n/a | n/a |
| **Software for data management:** | SAS 9.4, My SQL 15.0.2000.5 | SAS 9.4, My SQL 15.0.2000.5 |

*CDM = Common Data Model

- 1. Data management

The research team operates a secure, state-of-the-art, computing facility. The computer cluster is Linux-based and offers SAS 9.4, Stata 15.1, and R. The data center is a secure facility that houses both our computing environment as well as clinical systems and electronic medical records for several large hospitals in WA. Entry into the computer room requires passing through staffed building security, a successful palm scan, and then passing through staffed computer room security. The research machines are connected to the networking backbone with 10 gigabit-per-second fiber links. Network security is overseen by Information Security, who apply the same standards used for the hospitals electronic medical records systems to the research teams data. All data are transmitted to programmers' workstations in an encrypted state. Backups are created using 256-bit AES encryption, the current Department of Defense standard for data security, and are stored in a locked facility.

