#### Table 7. Operational Definitions of Outcome

| **Outcome name** | **Details** | **Primary outcome?** | **Type of outcome** | **Washout window** | **Care Settings¹** | **Code Type^2^** | **Diagnosis Position^3^** | **Applied to study populations:** | **Outcome measurement characteristics/**  **validation** | **Source of algorithm** |
| --- | --- | --- | --- | --- | --- | --- | --- | --- | --- | --- |
| Overall Survival |  | Yes | Time-to-event | n/a | n/a | n/a | n/a | Exposure, comparator 1, comparator 2 | The positive predictive value of death in XYZ Registry is 96%. Sensitivity is 93%. | Hospital records + registry validation |
| Progression-free survival |  | No | Time-to-event | n/a | n/a | n/a | n/a | Exposure, comparator 1, comparator 2 | Unknown | (still in discussion) Derive variable from hospital pharmacy data + lab/report/imaging + toxic side effects + time to treatment failure |
| HRQoL (generic) |  | No | Continuous, categorical, binary | n/a | n/a | n/a | n/a | Exposure, comparator 1, comparator 2 | EQ-5D-5L is a validated instrument widely used in oncology (Schwenkglenks 2016 Expert Review of Pharmacoeconomics and Outcomes Research) | EQ-5D-5L |
| HRQoL (disease-specific) |  | No | Continuous, categorical, binary | n/a | n/a | n/a | n/a | Exposure, comparator 1, comparator 2 | EORTC-CXX and EORTC-CXY are validated widely used instruments ([name] 2021, European Journal of Cancer) | EORTC-CXX and EORTC-CXY |
| Toxic side effects |  | No | Time-to-event | n/a | n/a | n/a | To be discussed | Exposure, comparator 1, comparator 2 | To be discussed | To be discussed |
| Resource use |  | No | To be discussed | n/a | n/a | n/a | n/a | Exposure, comparator 1, comparator 2 | To be discussed | To be discussed |

^1^ IP = inpatient, OP = outpatient, ED = emergency department, OT = other, n/a = not applicable

^2^ See appendix for listing of clinical codes for each study parameter

^3^ Specify whether a diagnosis code is required to be in the primary position (main reason for encounter)

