#### Table 8. Operational Definitions of Follow Up

|  |  |  |  |
| --- | --- | --- | --- |
| **Follow up start** | Day 1 |  |  |
| **Follow up end^1^** | **Select all that apply** |  | **Specify** |
| **Date of outcome** | Yes |  | See Table 5 |
| **Date of death** | Yes |  | Discharged dead or registry recorded death, whichever came 1st |
| **End of observation in data** | Yes |  | Allow 30 day gaps in enrolment |
| **Day X following index date**  *(specify day)* | Yes |  | Day 365 |
| **End of study period**  (specify date) | Yes |  | 30-Sep-15 |
| **End of exposure**  *(specify operational details,*  *e.g. stockpiling algorithm, grace period)* | Yes |  | **Stockpiling algorithm:** If refill occurs before end of days supply, count overlapping days at the end of the subsequent dispensing’s day supply.  **Grace period:** Bridge gaps of ≤30 days between dispensation + days supply and refill. Add 30 days to last dispensation + days supply in a treatment episode. |
| **Date of add to/switch from exposure**  *(specify algorithm)* | Yes |  | Date that patient in exposed group is dispensed comparator drug or vice versa |
| **Other date** *(specify)* | Yes |  | Nursing home admission |

^1^ Follow up ends at the first occurrence of any of the selected criteria that end follow up.

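### Table 12 ties registry release to cohort (V1.0 historical, V2.0 to V5.0 for Drug A/B), so any release difference in capture could not be separated from treatment in the historical comparison

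*Protocol*

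**What the plan says.** Table 12 describes two data sets from the same registry. Its Data Version row reads "V2.0 – V5.0 | V1.0", the first entry for the concurrent/prospective data and the second for the historical data.

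- The concurrent set (2021-2022) covers patients who "are treated with a combination of Drug A/B or with standard care", so Drug A/B and concurrent SoC share V2.0 to V5.0.
- The historical set has study and entry period "Jan 1, 2019- Dec 31, 2020" and holds SoC patients only, all from V1.0.
- Both columns give the same content ("Patient registry data including linked electronic health records, insurance claims, death, and patient reported outcomes") and the same identifier linkage.

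Table 2 plans, for every objective, a second comparator group "using historical controls from years of data prior to availability of Drug A/B". Table 10 specifies the primary analysis and secondary analysis 1 against comparator 1 (concurrent) only; it contains no historical analysis.

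On deaths, Table 7 states "The positive predictive value of death in XYZ Registry is 96%. Sensitivity is 93" per cent, without naming a release or period. Table 8 applies one rule to all groups: "Discharged dead or registry recorded death, whichever came 1st".

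**The concern.** In a Drug A/B versus historical comparison, every treated patient comes from V2.0 to V5.0 and every comparator from V1.0. Release is then fully aligned with treatment, as calendar period already is. If releases differ in how completely they hold deaths, claims or linkage corrections, nothing in the data can separate that difference from a treatment effect. Propensity score matching does not help, because the matching covariates come from the same two releases.

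Two of the plan's own rules carry incomplete capture into the estimate. Under Table 8, a death absent from the records is analysed as survival. Under the missing-data rule in Table 10, a condition with no claim is taken as absent, so a claim missing from one release becomes a misclassified covariate and not a missing value. Table 11 has no sensitivity analysis filled in yet, and Section 8 (limitations) does not mention release.

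At stake is the historical evidence for each objective, overall survival included. The planned effect is modest (hazard ratio 0.90 in Section 7.9), so a small difference in death capture could be of similar size.

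**Working it through.** **1. Which comparisons are exposed to the split**

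| Comparison | Drug A/B release | Comparator release | Release aligned with treatment? |
| --- | --- | --- | --- |
| Table 10: Drug A/B vs comparator 1 | V2.0 to V5.0 | V2.0 to V5.0 | No V1.0 split |
| Table 2: Drug A/B vs historical | V2.0 to V5.0 | V1.0 | Fully |

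**2. The plan's own figure**

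The protocol gives no figure for release differences. Its only related calculation is the power statement in Section 7.9, which reproduces. With 5,000 exposed matched 1:1 and 35% deaths, events = 10,000 × 0.35 = 3,500. Taking two-sided alpha 0.05 (implied by the 95% interval), power = Φ(|ln 0.90| × √3,500 / 2 − 1.96) = 87.6%, against a stated figure of more than 80%. This does not bear on the release question; it confirms that 35% and 0.90 are the planning values.

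**3. Illustration of sensitivity to death capture**

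Inputs from the protocol: one-year risk of death 35% (Section 7.9), taken here as the SoC risk; hazard ratio 0.90 (Section 7.9); death sensitivity 93% (Table 7).

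Assumptions: 93% holds in V2.0 to V5.0, and V1.0 differs by 3 or 5 points either way. Falsely recorded deaths and censoring before one year are ignored.

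Formulas:
- True Drug A/B risk = 1 − 0.65^0.9 = 0.3214.
- Observed risk = sensitivity × true risk.
- Observed HR = ln(1 − observed Drug A/B risk) / ln(1 − observed SoC risk).

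Drug A/B side: 0.93 × 0.3214 = 0.2989, and ln(1 − 0.2989) = −0.3551.

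| V1.0 sensitivity | Observed SoC risk | ln(1 − risk) | Observed HR, true 0.90 | Observed HR, true 1.00 |
| --- | --- | --- | --- | --- |
| 0.88 | 0.3080 | −0.3682 | 0.964 | 1.070 |
| 0.90 | 0.3150 | −0.3783 | 0.939 | 1.041 |
| 0.93 (equal) | 0.3255 | −0.3938 | 0.902 | 1.000 |
| 0.96 | 0.3360 | −0.4095 | 0.867 | 0.962 |
| 0.98 | 0.3430 | −0.4201 | 0.845 | 0.937 |

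With equal sensitivity the distortion is negligible (0.902 for 0.90). A 5-point gap moves 0.90 to 0.964 or 0.845. On the log scale, −0.105 becomes about −0.037 or −0.168.

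**The case against.** The strongest reply is that the documents show version labels and nothing more. Registry, data types, linkage, software and death definition are the same in both columns, and V1.0 followed by V2.0 to V5.0 may simply be successive releases as the registry accrues. Sections 7.6.1 and 7.8 also point to external documentation of provenance and quality assurance, which may describe the releases. All of this stands, and it rules out four stronger readings that a reader might infer:

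- **That deaths and covariates are in fact captured differently by arm.** The protocol does not say so.
- **That the bias runs against Drug A/B because V1.0 is an early, incomplete cut.** V1.0 is undated. The historical period closed on 31 December 2020 and the data freeze in Table 1 is 1 March 2022, so V1.0 may be mature. Concurrent entry runs to 31 December 2022 with a final report on 1 September 2023, so the less mature data could be the Drug A/B data. That would bias in the other direction.
- **That the primary analysis is compromised.** Table 10 uses comparator 1, which shares V2.0 to V5.0 with Drug A/B.
- **That listing four releases puts concurrent patients on different cuts.** Later releases may be cumulative, with only the last one analysed. The table does not say.

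What the reply does not remove is the alignment itself. Table 12 states the split as a choice, where many other entries are left to be discussed, and Table 2 commits to the historical comparison. Ordinary successive releases still leave the historical comparators on the first one and the treated patients on later ones.

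**Conclusion.** The point holds as a design weakness confined to the Drug A/B versus historical comparison, which Table 2 plans for every objective and for which Table 10 has no analysis yet. In that comparison a release effect could not be told apart from a treatment effect, and the protocol states no safeguard.

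Its size cannot be taken from the documents. Under the assumed 5-point gap in death sensitivity, a true hazard ratio of 0.90 would be seen as about 0.85 or 0.96, and a true 1.00 as about 0.94 or 1.07. If capture is equal, there is essentially no distortion. The range shows only that a gap of a few points would be comparable with the planned effect. It is not an estimate of bias in this study.

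This should be changed before registration because it is inexpensive, but it does not threaten the analyses now specified in Table 10.

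**What to change.** 1. In Table 12, name one common release for all three populations, namely the latest one used for the final analysis, and re-extract the 2019-2020 comparators from it.
2. If that release does not hold the 2019-2020 patients with equivalent fields, which the documents leave open, state what differs between releases and show death and covariate capture by release before interpreting any historical comparison.
3. In Table 7, state the release and period to which the 96% positive predictive value and 93% sensitivity apply.

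The cost is one re-extraction and some added data checks. A common release removes the release difference only; the difference in calendar period between the historical and Drug A/B patients remains and has to be handled separately.
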